**Discussion:**

We hypothesise that the improvement in digit span backwards after 12 weeks of treatment will be significantly higher in the group treated with the combined cognitive-motor telerehabilitation programme, compared to the groups receiving only cognitive and only motor training.

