**Fig. 1 Fig1:**
[figure not shown]
Trial flowchart

Patients in the cognitive-motor training group will carry out both the cognitive and the motor training programme, while patients in the cognitive training group and the motor training group will respectively carry out only the cognitive training programme and the motor training programme (see Fig. 1). Before the start of the training, a start-up teleconsultation with an MS nurse will be scheduled, where patients will receive clear instructions on how to carry out the training programme(s).

For the cognitive treatment intervention, we will use the widely used cognitive training programme RehaCom® (Hasomed GmbH, Magdeburg, Germany). This is a computer-aided programme with more than 30 modules focusing on different domains of cognition. RehaCom has shown improvements in verbal learning, visuospatial memory, information processing speed, attention, executive functions, depression, fatigue and quality of life in PwMS [35–38]. Patients will train on their home computer without direct therapist supervision, using three RehaCom modules (Working Memory, Topological Memory and Shopping) that are focused on improving working memory. Both patients in the combined intervention and the cognitive intervention group will be doing a 45-min computer session respectively 1 and 2 days per week for a total of 12 weeks. During one 45-min training session, patients will complete 15 min of exercises of each of the three modules. The level of difficulty of the exercises is automatically adapted to the patient’s performance.

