For the motor training, we will use a patient-tailored training programme based on the patient’s baseline activity level. At inclusion, all patients will complete the Godin Leisure-Time Exercise Questionnaire (GLTEQ) to assess their level of activity and be divided into three groups (see Fig. 2) [39]. Based on their baseline physical activity level, patients can choose from a number of aerobic activities of either mild, moderate or strenuous intensity, with a total training time of 90 min per week for the motor training group and 45 min for the combined cognitive-motor training group, divided over at least two training sessions per week of at least 15 min per session (see Fig. 2). The training will be carried out individually at home, without therapist supervision. Patients will use a heart rate sensor to maintain the correct training intensity, with 20–39%, 40–59% and 60–84% of their heart rate reserve (target heart rate = *heart rate reserve*X% intensity + resting heart rate; heart rate reserve* = *maximum heart rate − resting heart rate*; *maximum heart rate = 220 − age* [40]) respectively corresponding to mild, moderate and strenuous training [41–43]. Heart rate will be monitored using a sport watch (Polar Unite, Polar Electro, Kempele, Finland), provided by the research team and equipped with an accelerometer and a heart rate sensor. Furthermore, patients will be asked to rate the training intensity with the Rating of Perceived Exertion scale (RPE [44]). A score of 10–11, 12–13 and 14–16 corresponds to mild, moderate and strenuous training respectively [41, 42]. Both baseline activities and training activities in the context of the study will be logged using the sports watch. In order to ensure that activity levels remain the same in the group receiving only cognitive training, the activity levels of these patients will be monitored as well. Adaptations to training intensity in response to issues reported by patients will be decided on a case-by-case basis.

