**Fig. 2 Fig2:**
[figure not shown]
Motor training algorithm

Participants will have a 20-min teleconsultation once every 2 weeks with a trained MS nurse. The teleconsultations will take place using Microsoft Teams® (Microsoft Corporation, Redmond, WA, USA) and the patient can use any device equipped with a webcam and microphone. The consultations consist of a structured interview dealing with motivation of the patient to continue the training, perceived impact of cognitive and physical difficulties on the patient’s life in the past weeks, effort applied to the training in the previous weeks, technical difficulties experienced, targets for next weeks’ training, and additional questions by the patient. Adherence to the training programmes will be assessed through a RehaCom therapist account for the cognitive training and through a Polar Flow for Coach account for the motor training.

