### Blinding and statistical methods

The study will be blinded: patients will not be made aware of the rationale and predictions of the study (pseudo-blinding). The randomisation procedure and the teleconsultations will be carried out and communicated to participants by a trained MS nurse, while the baseline and follow-up testing and analyses are carried out by an investigator who is blinded to the treatment allocation of the patients. Unblinding will only be done in the unlikely case of serious adverse events.

Differences between the different treatment groups in the clinical endpoints compared to baseline will be assessed with a one-sided ANOVA repeated measures test with a within-between interaction. A type I error probability of 0.05 will be used for the main effects and interaction effects. We will correct for multiple comparisons in the post hoc analyses via a family-wise error rate. Per-protocol analyses will be performed, and to correct for missing data, analyses will be repeated using the last observation carried forward method. In case of dropout before the second follow-up testing at 24 weeks, the differences in clinical endpoints at week 12 compared to baseline will still be assessed.

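### Per-protocol is the only analysis set named for a superiority comparison; its criteria are not given and no analysis of all randomised patients as allocated is stated

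*Protocol article*

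**What the plan says.** The section on blinding and statistical methods states the analysis population in four words of substance: "Per-protocol analyses will be performed". The same sentence adds that, "to correct for missing data, analyses will be repeated using the last observation carried forward method". The next sentence deals with late dropout and keeps the week-12 comparison for such patients; it begins "In case of dropout before the second follow-up testing at 24 weeks, the differences in clinical endpoints at week 12 compared to baseline will still". No intention-to-treat, full or all-randomised set appears anywhere in the article, and no rule says who belongs to the per-protocol set.

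The hypothesis in the abstract is one of superiority: improvement in digit span backwards "will be significantly higher in the group treated with the combined cognitive-motor telerehabilitation programme" than in either single-training group.

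The section on intake and intervention describes home training. For the cognitive part, "Patients will train on their home computer without direct therapist supervision"; for the motor part, "The training will be carried out individually at home, without therapist supervision". Compliance is tracked during the trial: "Adherence to the training programmes will be assessed through a RehaCom therapist account for the cognitive training", with a separate account for the motor training.

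**The concern.** In a superiority trial, randomisation protects the comparison of all patients in the arms to which they were allocated. A per-protocol set is ordinarily formed by removing patients for what they did after randomisation, such as training too little. If the share removed, or the kind of patient removed, differs by arm, the remaining groups are no longer comparable and the difference between them is not purely a treatment effect.

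Non-adherence is foreseeable when training is done at home without a therapist present, and the three regimens are not alike. The combined and cognitive groups "will be doing a 45-min computer session respectively 1 and 2 days per week for a total of 12 weeks", and the combined group adds exercise sessions to its single computer session. Different exclusion rates are therefore possible. With no written criteria, the choice of who is analysed also stays open.

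Two things are at stake: the validity of the primary comparison, and a sample size that has no room for exclusions.

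**Working it through.** **1. Does another sentence supply an all-randomised analysis?**
- Last observation carried forward fills in a missing score. A patient who trained little but came for the post-training test has no missing score, so nothing in the stated purpose of the repeat brings that patient back into the analysis.
- The late-dropout sentence keeps patients who leave before the 24-week test in the week-12 comparison. It does not deal with non-adherence or with loss before the post-training test.
- Neither sentence states an analysis of all randomised patients as allocated.

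**2. Reproducing the plan's sample size.** Inputs from the sample size section: repeated-measures ANOVA with within-between interaction, alpha 5%, power 95%. There are k = 3 groups, and m = 2 measurements (pre and post) is the reading that returns both stated totals. The test statistic follows a noncentral F distribution with

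λ = f² × N × m / (1 − r), df1 = (k − 1)(m − 1) = 2, df2 = (N − k)(m − 1) = N − 3.

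- f = 0.40, r = 0.50: required N = 30, power 96.8%. This matches the stated 30.
- f = 0.25, r = 0.30: λ = 0.0625 × 90 × 2 / 0.70 = 16.07; required N = 90, power 95.1%. This matches the stated 90.

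So 90 is the number needed in the analysis, and it is also the number to be randomised.

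**3. Power if a per-protocol set removes patients.** Same formula with f = 0.25 and r = 0.30. The exclusion rates are assumptions; the document gives none.

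| Excluded (assumed) | Analysed | λ | Power | Randomised to keep 90 |
|---|---|---|---|---|
| 0% | 90 | 16.07 | 95.1% | 90 |
| 10% | 81 | 14.46 | 92.6% | 90 / 0.90 = 100 |
| 20% | 72 | 12.86 | 89.1% | 90 / 0.80 = 112.5, so 113 |
| 30% | 63 | 11.25 | 84.2% | 90 / 0.70 = 128.6, so 129 |

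**4. How the bias arises.** Let p be the share excluded in an arm and g the mean outcome gap between retained and excluded patients. The mean of all patients is the retained mean minus p × g, so the per-protocol mean is shifted by p × g. With the same g in two arms, the bias in their difference is (p1 − p2) × g.

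- Assume 25% excluded in one arm and 10% in the other, with g from 0.3 to 1.0 SD. The bias is 0.15 × 0.3 = 0.045 SD to 0.15 × 1.0 = 0.15 SD in favour of the arm with more exclusions. Swapping the arms reverses the sign.
- With equal p and equal g the bias is zero.

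**5. Effect on type I error, as an illustration.** Assume no true effect, a correlation ρ of 0.2 to 0.4 between adherence and change, and retention of 90% in one arm and 70% in the other (27 and 21 of 30). Under a normal model the mean of those retained is ρ × φ(q) / (share retained), where q is the cut-off on adherence. This is 0.195ρ at 90% and 0.497ρ at 70%. The spurious difference is 0.302ρ, which is 0.06 to 0.12 SD. The standard error is √(1/27 + 1/21) = 0.291. A one-sided 5% pairwise test in favour of the more selected arm then rejects about 7.5% to 11% of the time.

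**The case against.** A condensed article need not define its analysis sets, and the criteria may stand in a fuller document. That is fair as to the definition. It does not cover the choice itself: the article states which set will be used, and it names only that one.

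The sentence also has a milder reading. A repeat that fills missing scores makes most sense if the first analysis is of completers and the repeat restores dropouts; patients who stopped training but were tested might then stay in both. The text does not rule this out. Even so, the all-patient version would be only a repeat, and for someone with no post-training score it would carry the baseline forward and assume no change.

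A reader might go further and infer that the plan excludes patients below an adherence threshold, that those excluded would have done worse, and that the combined arm gains from it. The documents do not support this:
- No threshold is written. The article says only that adherence is assessed, so selection on adherence follows from the usual meaning of per-protocol, not from a stated rule.
- Nothing is said about the prognosis of non-adherent patients.
- Every arm trains 90 minutes a week. The motor arm exercises for 90 minutes against 45 in the combined arm, so poorer adherence in the motor arm is just as plausible.
- The training is unsupervised but not unsupported: a nurse holds a teleconsultation every two weeks on motivation, effort and targets.

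**Conclusion.** The point stands in this form: for a superiority question, the article commits to per-protocol as its only named set, gives no criteria for it, and states no analysis of all randomised patients as allocated. Bias is possible in either direction. Its size cannot be calculated from the document, and it vanishes if exclusion and selection are the same in each arm; the bias and type I error figures above only illustrate the mechanism under assumed inputs.

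The power loss is the lesser matter. It rests on assumed exclusion rates and holds f at 0.25 throughout. Keeping non-adherent patients may itself dilute the effect, so an all-randomised analysis of 90 does not guarantee 95% power either. The correction should still be made before analysis, because the primary claim rests on this set.

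**What to change.** State that the primary analysis includes all randomised patients in the arm to which they were allocated, regardless of adherence, and uses every available digit span backwards assessment in a mixed model for repeated measures with group, time and their interaction. The change of model is part of the fix: repeated-measures ANOVA in its usual form drops a patient with a missing visit, so it cannot deliver an all-randomised analysis. The mixed model relies on scores being missing at random, and that assumption should be stated.

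Keep the already scheduled assessments for patients who stop training. Report per-protocol as a sensitivity analysis, with its criteria fixed in advance.

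The cost is wording in the protocol and analysis plan, a different model, and the effort of bringing patients who stop training to visits that are already planned. The estimated effect may be slightly smaller because non-adherent patients are kept. The required number analysed, 90 on the plan's own calculation, does not change.

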### Primary outcome parameter

The primary outcome measure is the digit span backwards test [33], which assesses working memory. The examiner produces a list of digits at a rate of one digit per second and patients have to repeat the list in reverse order. Two trials are presented for each span length. If patients fail two trials of the same span length, the test is ended. The test starts with a list of two items and gradually increases to a maximum of eight items. Based on clinical experience, we will consider an improvement of one point on this test a clinically significant difference. This test will be carried out at the start of the trial, after 12 weeks of training, at 24 weeks and 64 weeks.

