### Sample size

We calculated the minimal sample size with G*Power [61], using an ANOVA design (repeated measures, within-between interaction) with a power of 95% and an alpha error rate of 5%. Under the assumption of a large effect size (*f* = 0.40, based on the change in digit span backwards score after cognitive training [62]) and moderate correlation between the pre- and post-training measurements (*r* = 0.50), the required sample size is 30. Under the less favourable assumption of a medium effect size (*f* = 0.25) and a small correlation among repeated measurements (*r* = 0.30), the required total sample size is 90. In this study, we chose a total sample size of 90, with 30 subjects in each group.

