Research on combined cognitive-motor training in multiple sclerosis is still lacking. Our trial is unique since it is the first to compare the effect of combined cognitive-motor training to both single cognitive and single motor training on cognition in MS. Furthermore, the training is completely home-based, thereby eliminating transportation and reducing therapist time, while enabling the patient to carry out the training independently at any time of the day. These advantages increase the potential applicability of this intervention in daily practice. Finally, our study will include a large sample of PwMS, with both a relapsing-remitting and progressive disease course, and collection of data on long-term follow-up, mechanisms of improvement and predictors of treatment response.

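### Last observation carried forward is the only stated correction for missing data; it gives early dropouts exactly zero change and assumes later dropouts keep their full post-training score

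*Protocol article*

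**What the plan says.** The section on blinding and statistical methods covers missing data in two sentences. The first plans per-protocol analyses and adds that "to correct for missing data, analyses will be repeated using the last observation carried forward method". The second covers patients lost between the post-training and 24-week tests: their week-12 change from baseline is still analysed. The model is a repeated-measures ANOVA; group differences in change from baseline "will be assessed with a one-sided ANOVA repeated measures test with a within-between interaction".

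Digit span backwards, the primary measure, is tested at the start and again "after 12 weeks of training, at 24 weeks and 64 weeks" (Primary outcome parameter). Training ends at week 12, and the schedule table puts the post-training test at week 13. The registration data set defines the primary outcome as the change from before to after treatment. The Discussion lists "collection of data on long-term follow-up" among the trial's strengths.

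**The concern.** LOCF does not recover missing information. It replaces each missing score with a particular assumption, and here the assumption differs by time of loss.

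- **Lost before the post-training test.** The only score is baseline, so the imputed change is zero. Retested patients may gain from training, from practice, and from regression to the mean after selection on a low digit span score. Patients lost early are denied all three, and their zeros enter the primary contrast.
- **Lost after the post-training test.** The score taken just after training is carried to weeks 24 and 64. That assumes full retention for about a year (week 13 to week 64), and retention is what the later visits can show.

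LOCF is the only correction named, so it is the only stated way for patients without a post-training score to enter the comparison. A per-protocol analysis, as usually understood, does not represent patients who leave during training. At stake are the primary contrast, if patients leave during training, and any statement about durability, if they leave afterwards.

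**Working it through.** **Inputs from the article.** Three arms of 30; tests at baseline, after training, week 24 and week 64; 1 point on digit span backwards taken as clinically significant.

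**Which contrast was planned.** The sample size was reproduced with the noncentral F distribution, λ = f²·N·m/(1 − r), with 3 groups, m = 2 measurements and alpha 0.05.
- f = 0.40, r = 0.50, N = 30: λ = 0.16 × 30 × 2 / 0.50 = 19.2, power 0.968.
- f = 0.25, r = 0.30, N = 90: λ = 0.0625 × 90 × 2 / 0.70 = 16.07, power 0.951.

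Both stated sizes come out exactly, and they did not with m = 3 or 4. The trial is sized for the pre-post contrast. Early dropout therefore touches the primary result, whereas late dropout touches only weeks 24 and 64.

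**Assumptions (not in the article).** Mean post-training gain of 1.5 points in the combined arm and 0.5 in a control arm, a true difference of 1.0. Dropout of 10% to 30%. Dropouts would on average have scored like those who stay.

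**(a) Early dropout.** With dropout d₁ (combined) and d₀ (control), the LOCF difference is (1 − d₁) × 1.5 − (1 − d₀) × 0.5.

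| d₁ | d₀ | LOCF difference (true 1.0) |
|---|---|---|
| 10% | 10% | 1.35 − 0.45 = 0.90 |
| 20% | 20% | 1.20 − 0.40 = 0.80 |
| 30% | 30% | 1.05 − 0.35 = 0.70 |
| 30% | 10% | 1.05 − 0.45 = 0.60 |
| 10% | 30% | 1.35 − 0.35 = 1.00 |

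If instead every arm gains 1 point, so that the true difference is 0, dropout of 30% against 10% gives 0.70 − 0.90 = −0.20, which is unrelated to training.

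**(b) Late dropout.** If a fraction ρ of the gain is kept at week 64, the LOCF difference is [(1 − d₁)ρ + d₁] × 1.5 − [(1 − d₀)ρ + d₀] × 0.5.

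| d₁ | d₀ | ρ = 0 (true 0) | ρ = 0.5 (true 0.50) |
|---|---|---|---|
| 10% | 10% | 0.10 | 0.55 |
| 20% | 20% | 0.20 | 0.60 |
| 30% | 30% | 0.30 | 0.65 |
| 30% | 10% | 0.40 | 0.70 |
| 10% | 30% | 0.00 | 0.50 |

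Under equal late dropout d the bias is d × (1 − ρ) × (post-training difference). It is zero if gains persist (ρ = 1) or if the arms never differed.

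**(c) Effect on error rates.** Simulated trials with 30 per arm, correlation 0.5 and nominal 5%, testing change from baseline across the three arms:
- Benefit fully lost by week 64, assumed SD 2 points: about 6% to 7% rejection at 20% late dropout and about 8% at 30%, against about 5% using available cases.
- Equal true gains of 1 point, SD 2 points, early dropout of 30%, 10% and 10%: about 7%.
- Equal gains of 1 SD fading to 0.3 SD, 20% late dropout in every arm: every arm's week-64 mean is too high (0.8 × 0.3 + 0.2 × 1.0 = 0.44 SD), but rejection stays at 5%.
- Equal gains of 0.5 SD, 20% early dropout in every arm: about 4.6% at the post-training test.

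**The case against.** The best defence is that LOCF is a repeat beside another analysis, and that the sentence on dropout before 24 weeks keeps observed post-training scores. Both statements are correct and limit the point. That sentence means it would be wrong to infer that the ANOVA discards every incomplete patient: for the pre-post comparison, those lost after the post-training test stay in. It does nothing for patients with no post-training score, and it leaves weeks 24 and 64 untouched.

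A reader might also infer three stronger things that the article does not support.
- *That LOCF overstates long-term retention.* This follows only if gains fade. The article gives no retention figure and states no hypothesis about decay.
- *That LOCF biases the comparison of arms in any event.* Bias in the contrast needs unequal dropout or arm-specific gains. If gains at each visit and dropout are equal, it is zero, even where each arm's own mean is wrong.
- *That treating imputed values as observed makes standard errors too small and inflates type I error in general.* The simulations with equal arms stay at or slightly below 5%. The problem is biased means when arms differ.

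It is also fair to say that the primary hypothesis concerns change after 12 weeks, which carry-forward to weeks 24 and 64 cannot affect. And someone who stops training early may truly gain little. In that case zero change is nearer the truth, but it remains an assumption imposed without a check.

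**Conclusion.** The point stands in limited form. LOCF is the sole stated correction for missing data and it does not correct. It fixes early losses at zero change, within the primary contrast, and assumes full retention for later losses, at weeks 24 and 64. The bias can go either way, so LOCF cannot be defended as conservative.

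Under the assumed gains and equal dropout of 10% to 30%, a true 1-point post-training difference is reported as 0.90 to 0.70, and a benefit that has vanished by week 64 is reported as 0.10 to 0.30 points. Unequal dropout of 30% against 10% widens these errors to 0.40 points in one direction and happens to cancel them in the other. In the scenarios simulated, type I error rises only modestly.

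The mechanism follows from the method and the visit schedule. The sizes rest on assumed dropout, gains and retention, none of which the article supplies. The change is worth making before unblinding, but nothing here shows that the trial's primary result would be invalid.

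**What to change.** Delete LOCF. Analyse all randomised patients with a likelihood-based longitudinal model on every observed visit: baseline included as an outcome, a common baseline mean across arms, arm-by-visit effects and an unstructured covariance. This is valid if data are missing at random. Baseline should be an outcome rather than a covariate, because a model that only adjusts for baseline takes no outcome information from patients with no later visit, and they are the early dropouts at issue.

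Add one sensitivity analysis that departs from missing at random: multiple imputation with a delta shift for dropouts, over a range of shifts set in advance. Keep the per-protocol analysis as supportive.

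The cost is a change of wording and slightly more analysis work. No new data or visits are needed, and N = 90 is unchanged.
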